#### Sample Size Justification

We will have 80% power to detect a minimum hazard ratio of 1.53 per 1-s increase in stabilization time with a total sample size of 200 healthy participants, an event rate of 22%, and a standard deviation of 1 s using a Cox regression model at the 0.05 significance level. The event rate was estimated from the average number of athletes who experienced musculoskeletal injuries at the University of Utah from 2015 to 2018.

## Discussion

While a number of studies have examined static balance and gait after mTBI, reactive postural responses are an essential component of balance control for athletic performance and remain largely unstudied. An inability to accurately respond to postural disturbances could contribute to the increased musculoskeletal injury risk after mTBI. Therefore, the primary goal of this study is to determine if impaired reactive postural responses contribute to the increased musculoskeletal injury risk after mTBI. Using a two-phase approach, we will determine to what extent, and for how long, reactive postural responses are impaired after mTBI (phase 1), and we will determine the association between reactive postural responses and prospective musculoskeletal injury risk (phase 2). This study is unique in that it objectively measures reactive postural responses, an understudied component of balance, after mTBI.

Reactive postural responses are common in athletic competition and essential for athlete safety, but this domain of balance control has not been studied extensively after mTBI. Time to stability after dynamic movement can discriminate between those with history of mTBI and healthy controls (Lynall et al., 2020), suggesting that stability may be an important post-mTBI measure. However, no study has examined reactive postural responses in athletes with mTBI. We suspect the lack of knowledge concerning reactive postural responses after mTBI stems from two sources. First, reactive postural responses have been historically considered reflexive (subcortical) (Jacobs and Horak, 2007; Jacobs, 2014). However, it is likely that reactive postural responses rely on interaction among spinal circuits, the brainstem, and the cortex (Jacobs and Horak, 2007). As the focus of mTBI has traditionally been on cortical damage, postural responses may have been considered too automatic/reflexive to be disrupted by mTBI. The second possible reason for a gap in knowledge is logistical; traditional assessments of postural responses require sophisticated moving platforms (Zettel et al., 2008a,b) or tether-release (MacKey and Robinovitch, 2005; Inness et al., 2015) setups. Given some of the patient burden hurdles ingrained within clinical mTBI research, it is perhaps unsurprising that few studies have examined postural responses using these types of equipment. In fact, in designing this protocol, we considered implementing similarly controlled postural response paradigms (e.g., tether-release, moving platform, etc.). However, the need for a clinically feasible testing paradigm was critical to minimize the burden on student-athlete participants. Therefore, we selected the P&R test, a clinical test traditionally quantified using visual scoring. The notable weakness of this task is the relative simplicity for highly athletic individuals—few athletes should take multiple steps or struggle to recover. The use of wearable sensors is therefore essential and enables quantitative metrics of response latency, step length, and time to stabilization. The combination of wearable inertial sensors with the clinical P&R test facilitates assessments of reactive postural responses within an athletic training room with minimal added burden on the athlete. If we find athletes with recent mTBI take longer to regain stability or exhibit longer step latencies, it will provide evidence that mTBI impairs the reactive restoration of balance, demonstrating that mTBI affects all domains of balance control. Additionally, if we find differences between groups across time, it will support our hypothesis that postural responses are persistently impaired after mTBI. Such findings, coupled with the clinical feasibility of the P&R assessment, may spur the integration of postural response testing into the clinical management for mTBI. In the future, more work will be needed to develop outcome measures with established cutoff values for return-to-to play that could be incorporated into a testing battery.

The ability to carry out multiple tasks simultaneously, or to divide attention, is important in maintaining postural stability. Dual-task paradigms challenge the capacity for divided attention by requiring the participant to deal with competing cognitive and motor demands (Yogev-Seligmann et al., 2008). Because attentional capacity is limited, simultaneous performance of the tasks will cause a decline in one or both of the tasks (Posner and Boies, 1971; Kahneman, 1973). Correspondingly, dual-task deficits after mTBI during standing balance (Cavanaugh et al., 2005) and gait (Howell et al., 2013a, 2017) persist longer than motor tasks alone. If we find that reactive postural responses are impaired only in athletes with recent mTBI when performing a simultaneous cognitive task, it suggests that clinical evaluations of reactive balance control after mTBI should incorporate complex cognitive environments similar to gameplay. This finding would add support to existing literature demonstrating the need for dual-task assessments involving both physical and cognitive demands similar to those experienced during athletic competition.

A primary challenge in directly associating musculoskeletal injuries to underlying concussion deficits is adequate statistical power. To address this challenge, we considered the following to be true: if postural responses are associated with musculoskeletal within a population, the association will hold for a subgroup of that population. Therefore, if we find an association between reactive postural responses and the time to musculoskeletal injury in the general athletic population, irrespective of mTBI (phase 2), we expect that any impairment in reactive postural responses after mTBI will also associate with a faster time to injury. This assumption allows us to obtain adequate power for a longitudinal survival model within a reasonable timeframe (3 years). However, it does prompt a question about the validity of this assumption. The interpolation of a population-level association (all athletes) to a subgroup-level association (those with acute mTBI) will be directly tested by comparing the time to injury in athletes from phase 1 to test the validity of our assumption. Additionally, our concurrent two-phase approach will allow us to explore the association between changes in reactive postural responses from baseline-to-post-mTBI with time to injury using the small subset of athletes in which we will have baseline (pre-mTBI) and longitudinal post-mTBI measurements.

This study seeks to further our understanding of balance control after mTBI by examining a heretofore understudied, yet critically important aspect of balance, reactive postural responses. Through the innovative use of wearable sensor derived measures gathered during a clinical testing battery, the results of this study will improve our understanding of balance control post-mTBI and contribute to the foundation of relevant post-mTBI rehabilitation targets.

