### Phase 1: Characterization of Postural Responses After mTBI and Persistent mTBI-Related Deficits

#### Participants

For phase 1, 80 subjects will be recruited (40 athletes who experienced recent mTBI and 40 healthy teammate controls, matched on position and practice exposure). Sports medicine fellowship–trained team physicians with at least 10 years of training and clinical experience will diagnose mTBI based on history and physical examination, which is currently the gold standard. All subjects will be between the ages of 18 and 30 years and tested on site in the Athletic Training Clinics at the University of Utah. Informed written consent will be obtained from all participants.

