#### Assessment Procedures

For phase 1, athletes will be assessed at four time points: (1) within 48 h of mTBI (acute), (2) within 24 h of starting RTP protocol (PreRTP), (3) within 24 h of being medically cleared for RTP (PostRTP), and (4) ~6 months after injury (6Month). Assessments will take ~15 min and will be administered at the end of current Pac-12 CARE Affiliated Project (CAP) testing (Broglio et al., 2017). CAP testing is a tablet-based battery of measures that examine personal and family health history, neurocognitive assessments, neurological status, postural stability, symptoms, and oculomotor/oculovestibular function. Tests included in CAP testing are the Sport Concussion Assessment Tool, Fifth Edition; BESS; Brief Symptom Inventory 18; SAC; ImPACT; and EYESYNC (SyncThink, Palo Alto, CA) measures (Maruta et al., 2018). Assessments of matched control subjects will be tested within 24 h of the testing session of the athlete with mTBI. Return to play will follow guidelines set forth by the University of Utah Concussion Management Plan. Athletes will progress to RTP when, under the guidance of the physician and athletic trainer, the assessment battery including symptom assessment, ImPACT, and BESS has normalized. In the current study, athletes will be cleared to start RTP by only a limited number of team physicians.

Within 48 h from the time of the mTBI, informed written consent will be obtained from the athlete with mTBI and the matched control teammate. A total of 40 athletes with mTBI and 40 matched control athletes will complete assessments at four time points (Acute, PreRTP, PostRTP, 6Month). Each assessment will include questionnaires, clinical tests of function, and instrumented assessments of reactive postural responses (Table 1).

**Table 1 T1:** Questionnaires, surveys, and tests utilized in the present study with description of subject group (mTBI, control, both) and time point (Acute, PreRTP, PostRTP, 6Month, all).

**Validated Questionnaires**	**Purpose**	**Subject group**	**Time point**
Multidimensional fatigue inventory	Multiple domains of fatigue	Both	All
Pittsburgh sleep quality index	Sleep quality and disturbances and daytime dysfunction	Both	All
Injury-psychological readiness to return to sport scale	Confidence to return to play	mTBI	All
Return to sport after serious injury questionnaire	Motivation underlying return to play	mTBI	6 month
**Patient self-report**	**Purpose**	**Subject group**	**Time point**

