Questions adapted from the OSU TBI-ID	Concussion history	Both	Acute, 6 month
Questions regarding recent (<2 years) lower extremity musculoskeletal injury and surgery history	Lower extremity injury and surgery history	Both	All
Questions regarding return-to-learn progress	Return-to-learn	mTBI	All
Questions regarding medication use postconcussion	Medication use	mTBI	All
**Test**	**Purpose**	**Subject group**	**Time point**
Clinical reaction time (drop stick test)	Clinical reaction time	Both	All
Instrumented balance error scoring system	Static balance	Both	All
Push and release test	Reactive postural response	Both	All

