**Figure 2 F2:**
[figure not shown]
(Left) Support was released at time 0 (solid yellow). Step latency (blue dashed line) and time to stabilization (yellow dashed line) are marked.

Using data from the sensor on the investigator's hand, release of support (*t*_0_) will be identified when acceleration is >5% of gravity. Step latency will be calculated as the amount of time (seconds) from *t*_0_ to first foot movement. First foot movement will be detected when foot acceleration >7% of gravity and rotational rate is >7 degrees/s (El-Gohary et al., 2017). To determine step length (meters) of the first step, the double integral of acceleration of the foot from first foot movement to the next zero velocity instant will be calculated. Magnitude thresholds of 97.4 degrees/s for rotational rate and 0.8 m/s^2^ relative to gravity for acceleration will be used to determine the zero velocity instant (Rebula et al., 2013). Time to stabilization will be calculated as the amount of time (seconds) from *t*_0_ to stabilization. Stabilization will be detected when lumbar acceleration <7% of gravity and rotational rate <7 degrees/s, after the last step (El-Gohary et al., 2017).

The primary outcome measure will be time to stabilization. Secondary outcomes include step latency, step length, and the clinical score (number of steps) (Horak et al., 2009). The clinical score will be rated as follows: 0 = fall, 1 = recovers independently but takes more than 1 step, 2 = recovers independently with one step.

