#### Prospective Musculoskeletal Injury Risk

Acute lower extremity musculoskeletal injuries for each athlete in phase 2 will be prospectively tracked for 1 year from the date of their first team activity. Injury data will be queried from the athletes' electronic medical records documented by the University of Utah Athletic Training Staff and maintained for the Pac-12 Sports Injury Registry Management and Analytics Program. Injuries of interest will include any acute orthopedic injury of the lower extremity, pelvis, lumbar spine, or abdomen that resulted in time lost, including but not limited to joint sprains, musculotendinous strains, and fractures. Because abdominal and lumbar muscles are required for stability and movement control (Cholewicki et al., 1997), and the lumbar spine is a critical junction of postural control during sport with high musculoskeletal loads and compressive muscle forces, both lumbar spine and abdominal injuries will be included. Any injury that results in an athlete being unable to fully participate in training or match play will be considered a time loss injury (Fuller et al., 2007; Howell et al., 2018a). Overuse injuries and preexisting conditions will be excluded. The primary outcome measure will be time to first musculoskeletal injury. The number of injuries within 1 year and severity of injuries (time lost from a given injury) will be included as secondary outcomes.

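### The phase 1 comparison said to test carry-over to mTBI athletes directly names no postural measure, and 40 mTBI athletes can only explore the question

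*Protocol article*

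**What the plan says.** The opening of the Discussion gives the primary goal as learning whether impaired reactive responses contribute to the raised injury risk after mTBI. Phase 1 measures postural responses after mTBI. Phase 2 relates baseline responses to later injury in healthy athletes. The Discussion joins the two with an assumption: "if postural responses are associated with musculoskeletal within a population, the association will hold for a subgroup of that population". It concedes that statistical power is a main challenge, that the assumption is what makes adequate power attainable, and that its validity is open to question. It then says that the step from all athletes to the acute mTBI group "will be directly tested by comparing the time to injury in athletes from phase 1 to test the validity of our assumption".

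Injury ascertainment is set out under phase 2, Prospective Musculoskeletal Injury Risk: "Acute lower extremity musculoskeletal injuries for each athlete in phase 2 will be prospectively tracked for 1 year". That section gives the data source (athletic training medical records kept for a conference registry), the time-loss definition and the time origin (first team activity).

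For phase 1, Outcome Measures, Sample Size and Statistical Analysis contain only Push and Release measures. The one phase 1 item on musculoskeletal injury is in Table 1, for both groups at all time points: "Questions regarding recent (<2 years) lower extremity musculoskeletal injury and surgery history". The last phase 1 visit is about 6 months after injury.

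**The concern.** The assumption is about a slope: among athletes with mTBI, does a longer TTS go with earlier injury? The sentence that promises the test is about injury timing. It names no postural measure, comparator or model. Injury timing alone cannot settle the slope. Athletes with mTBI could be injured sooner for reasons unrelated to TTS. Equally, they could be injured no sooner than others while TTS still separates those at higher risk from those at lower risk.

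An association in a whole population need not hold in a subgroup. Here the step is wider still, from healthy athletes measured preseason to athletes measured after an acute mTBI. Neither phase estimates the association in the group named in the primary goal, so this sentence is the main check offered on the bridge between them. If the result is read as a direct test, a difference in injury timing, or its absence, could be taken to confirm or refute something it does not address.

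**Working it through.** **Inputs**
- Phase 2, Sample Size Justification: N = 200, event rate 22%, SD 1 s, hazard ratio (HR) 1.53 per 1 s, 80% power, significance level 0.05.
- Phase 1, Participants: 40 athletes with mTBI and 40 controls.
- Introduction: musculoskeletal injuries about twice as likely after mTBI.
- Assumed, because the article gives no phase 1 values: the same SD of 1 s, a one-year event rate between 22% and 44% in mTBI athletes, no dropout.

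**Reproducing the plan's figure.** For a continuous covariate in a Cox model, events needed = (1.960 + 0.842)² / (SD² × ln(HR)²).
- 7.849 / 0.4253² = 43.4 events, and 43.4 / 0.22 = 197.3, so N = 198.
- With 200 × 0.22 = 44 events, power = Φ(0.4253 × √44 − 1.960) = 80.5%.

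The figure reproduces with a two-sided test; a one-sided test would give 88%. A simulated Cox Wald test with N = 200 gave 78%.

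**The same association within the 40 mTBI athletes.** Power = Φ(0.4253 × √D − 1.960). The HR detectable with 80% power is exp(2.802 / √D).

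| One-year event rate | Events D | Power for HR 1.53 | HR detectable at 80% power | Expected 95% CI if true HR is 1.53 |
|---|---|---|---|---|
| 22% | 8.8 | 24% | 2.57 | 0.79 to 2.96 |
| 44% | 17.6 | 43% | 1.95 | 0.96 to 2.44 |

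- Simulated power for the two rows was 23% and 40%.
- The 44% bound doubles the proportion. Doubling the hazard gives 1 − 0.78² = 39%, which lies inside the range.
- If only about 6 months were observed, at half the 22% rate (an assumption), there would be 4.4 events and 14% power.
- Reaching 43.4 events would take about 198 mTBI athletes at 22%, or 99 at 44%.

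**Comparing two slopes.** SE of the difference in log HR = √(1/D₁ + 1/D₂). The ratio of HRs detectable with 80% power is exp(2.802 × SE).
- mTBI athletes against the 44 phase 2 events: SE = √(1/8.8 + 1/44) = 0.369, ratio 2.8; or √(1/17.6 + 1/44) = 0.282, ratio 2.2.
- mTBI athletes against phase 1 controls alone (40 × 0.22 = 8.8 events): SE = √(1/8.8 + 1/8.8) = 0.477, ratio 3.8; or √(1/17.6 + 1/8.8) = 0.413, ratio 3.2.
- If the true HR were 1.0 after mTBI and 1.53 in phase 2, power to see the difference would be 21% to 33%.

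**A plain comparison of mTBI with control athletes.** With HR 2 and 22% events in controls, events = 40 × (0.22 + 0.392) = 24.5. Power = Φ(ln 2 × √24.5 / 2 − 1.960) = 40%, and 66 events would be needed for 80%. A positive result would still say nothing about TTS.

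**The case against.** The strongest reply is that the sentence names no comparator, so reading it as mTBI against control supplies something the text does not say. The sentences around it concern impaired responses being associated with faster injury. Relating phase 1 athletes' postural responses to their injury times is therefore a natural reading. That stands. A reader might infer that the authors plan an analysis that cannot bear on the assumption, but the text supports only that the comparison as worded omits the postural measure.

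A reader might also infer that phase 1 athletes are excluded from injury tracking. The article does not support that. Phase 1 athletes are Division I athletes at the same university, so the same records plausibly cover them. The Discussion expects a small subset with both baseline and post-mTBI data, and those athletes are tracked through phase 2. Nothing says the Table 1 history questions are meant to supply time to injury. A full protocol or analysis plan, not shown, may give the source and model.

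The article claims no power for this analysis, so the figures above contradict no stated number. It is open about the power problem and describes the related baseline-to-post-mTBI analysis as exploratory. No formal hypothesis, named outcome or sample size depends on the sentence.

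What survives is the wording. The article claims a direct test, gives it no postural measure, describes injury tracking only for the other phase, and rests it on 40 mTBI athletes.

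**Conclusion.** The point holds in a limited form. As written, the comparison does not test the assumption it is said to test directly, and the article does not say how phase 1 injuries will be ascertained for it. Under the favourable reading, a TTS model within the 40 mTBI athletes has about 24% to 43% power for HR 1.53 per 1 s, from 8.8 to 17.6 events. With a true HR of 1.53, the expected 95% interval would include 1 at either end of that range. Such a result could neither validate nor refute the carry-over. These figures assume that phase 1 shares the phase 2 SD, that one-year event rates in mTBI athletes lie between 22% and 44%, and that nobody drops out. Dropout or shorter follow-up would lower the power.

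A reader should not infer that the phase 2 calculation is wrong, since it reproduces, or that any planned primary analysis is invalid. This is a should-fix matter of specification and strength of claim. It matters because the overall goal concerns injury after mTBI.

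**What to change.** - Apply the phase 2 medical-record query and time-loss definition to phase 1 athletes, with a stated time origin and follow-up window. The origin should not precede the TTS assessment used in the model.
- Replace the comparison of time to injury with a Cox model of time to first injury on post-mTBI TTS within the mTBI athletes, naming the assessment that supplies TTS. Report the hazard ratio with its confidence interval.
- Compare that hazard ratio with the phase 2 value, stating that only about a 2.2- to 2.8-fold difference would be detectable with 80% power. An interaction with phase 1 controls alone is a weaker choice: it would need about 3.2- to 3.8-fold and would not compare with the general-athlete association in question.
- Describe the analysis as exploring the assumption, and state that conclusions about injury risk after mTBI remain conditional on an assumption this study does not establish.

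The cost is a small amendment and a check that consent covers the record query. No extra visits are needed. The downside is a weaker stated claim.

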## Ethics Statement

Written informed consent was obtained from the individual(s) for the publication of any potentially identifiable images or data included in this article.
